## Statistical analysis

The Heartland Study is designed as a prospective cohort study with target recruitment of 2,000 pregnancies. Anticipated loss to follow-up is estimated at conservatively estimated at 20%, yielding approximately 1,800 analyzable maternal-infant dyads for the longer-term Phase 2 portion of the study. Based on prevalence estimates reported in prior studies [55–60], it is estimated that this will yield (all approximated) 180 preterm births, 288 cases of hypertensive disorders of pregnancy, 126 cases of gestational diabetes, 90 cases of fetal growth restriction, 54 cases of congenital anomalies/malformations, and 11 cases of stillbirth. The detectable R^2^ attributed to the herbicide exposure variable of interest from a multiple regression model fit to the primary outcome (gestational age) adjusting for 5 covariates (with combined R^2^ of 0.20 by covariates themselves), with 80% power and a type I error of 0.05, is 0.003. The detectable odds ratios for presence of secondary outcomes associated with a one standard deviation increase in the herbicide exposure variable of interest range between 1.3 and 1.7 (excluding stillbirth), with type I error set at 0.0083 to keep familywise error at 0.05 for secondary outcomes [61]. Thus, the study is powered to detect several meaningful associations between herbicide exposures of interest and pregnancy outcomes.

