## Challenges and anticipated responses

While the Heartland Study is anticipated to be a relatively large cohort of at least 2000 pregnancy dyads, it may still be underpowered to identify associations between herbicides and some rare outcomes, such as stillbirth and specific congenital anomalies. Aggregation of related outcomes may be used to improve power where appropriate. For example, it may be appropriate to evaluate fetal death as an aggregate variable including stillbirth and miscarriage, which occur on a spectrum. Related congenital anomalies may be aggregated to achieve statistical power if appropriate.

This study is poised to make an important contribution to the existing knowledge about herbicide concentration. There may be limitations in the ability to detect important seasonal variations in concentration and sensitive windows for exposure, although recurrent urine samples are being collected throughout pregnancy and aggregate batches by phases of the growing season will be evaluated. The study will utilize the latest advancements in analytic techniques for urine biomarker analysis, providing an objective assessment of concentration. Multi-exposure modeling will be used to examine the combined effects of herbicide exposure. Geographic estimates of exposure will be used to augment biomarker data and allow for a more multidimensional exposure assessment. Through combined application of the techniques, the Heartland Study will fill important gaps in knowledge about herbicide exposures in the Midwest.

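### The fixed 0.0083 level for secondary outcomes is valid, but Holm's step-down on the same six p-values keeps familywise error at 0.05 and never has less power

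*Protocol article*

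**What the plan says.** All the relevant figures are in the article's Statistical analysis section.

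- Case counts are projected for six outcomes: "180 preterm births, 288 cases of hypertensive disorders of pregnancy, 126 cases of gestational diabetes, 90 cases of fetal growth restriction", then "54 cases of congenital anomalies/malformations, and 11 cases of stillbirth".
- The secondary outcomes are powered "with type I error set at 0.0083 to keep familywise error at 0.05 for secondary outcomes". No other device for familywise control is named, and the clause cites a source that is not shown.
- The detectable odds ratios per standard deviation of exposure "range between 1.3 and 1.7 (excluding stillbirth"; no value is given for stillbirth.
- Under Challenges and anticipated responses, the article concedes that "it may still be underpowered to identify associations between herbicides and some rare outcomes, such as stillbirth", and suggests pooling stillbirth with miscarriage where appropriate.

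The words Bonferroni, single-step and six do not appear. The paragraphs that describe the models name no multiplicity procedure.

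**The concern.** If every secondary outcome is tested at 0.0083 whatever the others show, the share of an outcome already rejected is not used again. The unused shares buy no error control.

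The loss is greatest when several associations are real. The study hypothesizes just that: the design section lists hypertensive disorders, gestational diabetes, fetal loss, anomalies, shortened gestation and low birth weight percentile together. What is at stake is some power on preterm birth, hypertensive disorders, gestational diabetes, growth restriction and anomalies. The validity of the error control is not in question.

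**Working it through.** **1. Where 0.0083 comes from.** 0.05/6 = 0.00833, which matches. The nearby alternatives do not: 0.05/5 = 0.0100, 0.05/7 = 0.0071, and Sidak with six tests = 0.0085. Six outcomes carry case counts. Leaving stillbirth out would give 0.01, so stillbirth is apparently counted in the divisor.

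**2. The stated odds ratios.** The formula for a one-SD exposure in logistic regression is

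OR = exp[(z(1−α/2) + z(0.80)) / √(N·p·(1−p)·(1−R²))].

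Inputs from the article:
- α = 0.0083.
- N: the article has its follow-up "yielding approximately 1,800 analyzable maternal-infant dyads". A 20% loss from 2,000 would leave 1,600, so both values were run.
- p = cases/1,800: hypertensive disorders 288/1,800 = 16%, anomalies 54/1,800 = 3%, stillbirth 11/1,800 = 0.6%.

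Assumptions:
- Tests are two-sided (sidedness is not stated).
- Power is 80%, which the article states for the primary outcome ("with 80% power and a type I error of 0.05").
- R² is 0 or 0.20. The 0.20 is borrowed from the linear gestational-age model ("with combined R^2^ of 0.20 by covariates themselves"); the article does not give it for the logistic models.

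The z sum is 2.638 + 0.842 = 3.480. With N = 1,800 and R² = 0.20:
- hypertensive disorders: exp(3.480/√(1,800×0.16×0.84×0.8)) = exp(3.480/13.91) = 1.28
- anomalies: exp(3.480/√(1,800×0.03×0.97×0.8)) = exp(3.480/6.47) = 1.71

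| N | R² | Hypertensive disorders | Anomalies | Stillbirth |
|---|---|---|---|---|
| 1,800 | 0 | 1.25 | 1.62 | 2.87 |
| 1,800 | 0.20 | 1.28 | 1.71 | 3.25 |
| 1,600 | 0 | 1.27 | 1.67 | 3.06 |
| 1,600 | 0.20 | 1.30 | 1.77 | 3.49 |

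The second and third rows both round to the stated 1.3 to 1.7. The range is therefore reproduced, but the match does not show which inputs were used.

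**3. Holm against the fixed split.** Holm compares the ordered p-values with 0.05/6 = 0.0083, 0.05/5 = 0.0100, 0.05/4 = 0.0125, 0.05/3 = 0.0167, 0.05/2 = 0.025 and 0.05, and stops at the first non-rejection. The check used 400,000 simulated sets of six two-sided z-tests, with each true effect at its 80%-power size at 0.0083 and stillbirth null.

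| True effects | Fixed 0.0083 | Holm, independent | Holm, correlation 0.3 |
|---|---|---|---|
| one | 80% | 80.0% | 80.1% |
| two | 80% | 81.4% | not run |
| three | 80% | 83% | 83% |
| five | 80% | 87.6% | 86.7% |

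Hand check for two independent effects: power at 0.0100 is Φ(3.480 − 2.576) = 0.817, so about 0.017 of probability lies between the first and second thresholds. Holm reaches it when the other effect is rejected: 0.80 + 0.80×0.017 = 0.814.

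Simulated familywise error under Holm was at most 0.049 in every scenario. Under the global null it equals that of Bonferroni.

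**4. A common odds ratio of 1.3** for the five outcomes other than stillbirth, with stillbirth null (N = 1,800, R² = 0, independent tests):

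| Outcome | Fixed 0.0083 | Holm |
|---|---|---|
| Preterm birth | 76% | 81% |
| Hypertensive disorders | 93% | 95% |
| Gestational diabetes | 58% | 66% |
| Growth restriction | 42% | 51% |
| Anomalies | 23% | 31% |

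**5. Detectable odds ratios at later steps.** With N = 1,800 and R² = 0.20, the anomaly value falls from 1.71 to 1.65 at 0.0167 and to 1.61 at 0.025. Those levels are reached only after three and four other outcomes have been rejected, so these are conditional values and do not replace 1.71 for planning.

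**The case against.** The strongest reply is that 0.0083 occurs only in a power statement. A Holm plan would also be powered at its first step, 0.05/6, so the figure cannot show that step-down testing was ruled out. The full analysis plan is not shown and may name such a test. This stands as a limit: the single-step reading is an inference. But the article offers one level as what holds familywise error at 0.05 and names nothing further. One sentence settles the matter either way.

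Equal Bonferroni shares are valid. A reader might infer that the plan's error control is faulty; it is not.

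A reader might also infer that Holm recovers alpha wasted on stillbirth. It does not: the smallest p-value still faces 0.0083 with stillbirth in the divisor. Taking stillbirth out of the family is a separate and debatable choice. The article already discloses the low power there and offers aggregation with miscarriage, which would give that slot more events.

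Finally, a fixed level gives directly matching simultaneous confidence intervals for the odds ratios, and Holm has no equally simple counterpart. That is a real, small cost in a study that reports odds ratios.

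**Conclusion.** The point holds as an efficiency improvement. The fixed level of 0.0083 is valid, but Holm on the same p-values is never less powerful and keeps familywise error at 0.05 under any dependence.

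The gain per outcome is about nil with one true effect, 1 point with two, 3 points with three and 7 to 8 points with five. The last figure is the best case, because it needs five of the six outcomes to be truly associated, each at its 80%-power size; it should not be read as the expected gain.

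The conclusion assumes that 0.0083 is a single-step split over the six listed outcomes and that the unseen analysis plan does not already step down. The sizes assume two-sided tests and correlation of 0 or 0.3. The mismatch between 1,600 and 1,800 does not affect the alpha split, nor the gains in step 3, where each effect is set at 80% power. Multiplicity across herbicides and trimesters is a separate matter that neither method over six outcomes addresses.

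**What to change.** Unless the analysis plan already specifies a step-down test, add one sentence to the Statistical analysis section before the exposure-outcome analyses begin. It should say that the six secondary p-values are tested by Holm at 0.05/6, 0.05/5, 0.05/4, 0.05/3, 0.05/2 and 0.05, stopping at the first non-rejection. If a step-down test is already planned, the sentence should say so.

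Keep 0.0083 and the range 1.3 to 1.7, labelled as conservative first-step planning figures. Report the odds ratios with their usual or Bonferroni-adjusted intervals, and state which.

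The change needs no new data or participants and loses no error control. Its only cost is that the intervals will not correspond exactly to the step-down decisions.

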## Methods

### Recruitment

Hospitals located in one of the 13 Heartland Study region states (Arkansas, Illinois, Indiana, Iowa, Kansas, Michigan, Minnesota, Missouri, Nebraska, North Dakota, Ohio, South Dakota, or Wisconsin) will be recruited as affiliated clinical sites. Currently participating clinical sites include Indiana University School of Medicine- affiliated Hospitals in Indianapolis, Indiana; Franciscan Health Center in Indianapolis, Indiana; and Gundersen Lutheran Medical Center in La Crosse, Wisconsin, and University of Iowa in Iowa City, Iowa. Pregnant persons attending obstetric clinics affiliated with a clinical site hospital will be recruited, although other pregnant peopleliving in Heartland Study states are also eligible to participate.

The target enrollment is 2000 pregnant dyads. To evaluate the distribution of herbicide concentrations among Midwestern pregnancies, a target of 30% of participants will be recruited from rural areas, categorized as those areas outside of urban area centers according to US census designations [43]. Pregnant persons ages 18 or older at time of recruitment who are being seen at prenatal clinics and who are ≤ 20 + 6 weeks gestation will be recruited. Best clinical estimate of gestational age will be utilized for recruitment purposes [44]. Both singleton and twin pregnancies will be included. The other putative biological parent will also be invited to enroll as a secondary participant, subject to the primary participant’s consent. Exclusion criteria include the primary participant not being fluent in and/or able to fully understand, read, write, or speak the English or other approved languages, or inability to provide written informed consent. Trained study personnel will screen for eligibility, explain the study purpose and protocol, and administer informed consent. Approval for the Heartland Study protocol and procedures will be obtained from each clinical site hospital’s local governing Institutional Review Board. If materials are developed in other languages, such as Spanish, persons who are able to fully understand, read, write, or speak those languages will be eligible for enrollment.

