### Outcomes

Study hypotheses relate to maternal and fetal reproductive outcomes that have been previously found to be associated with herbicide concentrations during pregnancy in human or animal studies. The primary outcome of the Heartland Study is gestational age at birth. Key human and animal studies supporting these hypotheses have been detailed in Tables 1 and 2. Maternal outcomes that will be considered are pregnancy loss, preterm birth, hypertensive disorders of pregnancy, and gestational diabetes. For purposes of the study, miscarriage is defined as the delivery of a liveborn fetus or a fetus who experienced fetal death for any cause before 20 + 0 weeks’ gestation. A miscarriage is considered early if delivery occurs at < 14 + 0 weeks and late if it occurs at ≥ 14 + 0 weeks’ gestation. Stillbirth is defined as fetal death before delivery after 20 weeks’ gestation [50]. Preterm birth is defined as delivery of a liveborn or stillborn infant for any reason between 22 + 0 and 36 + 6 weeks’ gestation [51]. Spontaneous preterm birth is defined as delivery that occurs after spontaneous onset of preterm labor or premature rupture of the membranes (PROM) or fetal membrane prolapse. Preterm labor is defined as spontaneous uterine contractions before membrane rupture, documented cervical change of at least 1 cm dilation or effacement during the admission, or dilation > 2 cm or effacement > 80% on admission for contractions. PROM is defined as spontaneous rupture of the membranes before the onset of contractions, regardless of subsequent labor augmentation or cesarean delivery. Indicated preterm birth is defined as delivery after induction or cesarean delivery between 20 + 0 and 36 + 6 weeks’ gestation for obstetric, maternal, or fetal indications. The indication for the delivery will be recorded. A birth is considered spontaneous unless documented otherwise. Term birth is defined as delivery of a liveborn or stillborn infant for any reason at ≥ 37 + 0 weeks’ gestation.

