Primary fetal/newborn outcomes being evaluated are miscarriage, stillbirth, congenital anomalies/ malformations, fetal growth restriction, length of gestation, and birthweight. Secondary analyses may be performed to evaluate neonatal health status, including presence of respiratory distress syndrome, respiratory/ventilatory support, neonatal sepsis (confirmed/suspected, early/late onset), intraventricular hemorrhage, and infant discharge status. We are collecting buccal swabs which will be banked and plan to explore epigenetic changes associated with herbicide concentrations as well. We will plan the future epigenetic analyses based on techniques and methylated regions of interest that are cutting-edge and relevant at the time of those analyses. Specific plans for that future work are beyond the scope of this methods paper. The specific methods and hypotheses relating to the epigenetic analyses in the future will be detailed in papers arising from those analyses.

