Descriptive statistics, including appropriate parametric and semiparametric methods, will be used for continuous, binary, ordinal, and polytomous variables to describe characteristics of the cohort, exposures, and outcomes. We will examine the concentration data for appropriateness of cutoff values (quartiles, quintiles, high/low, etc.) or use as a continuous variable. Examples of statistical modeling approaches that we intend to utilize include least-squares linear regression, which will be used to describe the unadjusted associations between continuous outcomes (e.g., length of gestation or birthweight) and longitudinal exposure variable; and logistic regression, which will be used to describe the unadjusted association between a dichotomous outcome (e.g., diagnosis of pre-eclampsia or gestational diabetes, presence of congenital anomaly) and longitudinal exposure variables. Multivariate models will also be fit using suitable stratification and modeling adjustments for confounding and assessments of effect modification to evaluate associations between each outcome and multiple longitudinal exposures using methods appropriate to the structure of the data and analyses [62]. We will begin with simple multiple logistic regression models but will adjust to other appropriate models based on the data. To evaluate for the presence of exposure misclassification, an exposure matrix variable utilizing both biomarker and geospatially derived exposure estimates will be modeled with respect to each outcome [63].

Confounding variables have been determined a priori based on prior studies. Potential confounding factors to be considered are maternal age [64, 65], country of birth [66, 67], race/ethnicity [68, 69], height and preconception weight (including Body Mass Index) [70, 71], pregnancy weight gain [72, 73], marital status [64, 74], employment status [75, 76], socioeconomic status [77, 78], education level [78, 79], smoking status [80, 81], insurance coverage [82–84], alcohol use [85, 86], drug use, caffeine use [87], history of fetal loss and gestational age at loss [88], parity [89, 90], prenatal care [91], and rurality [92, 93]. As we will have residential address information, we will be able to explore the impact of location-based markers of social determinants of health such as distance to health care facilities, area deprivation, green space, and others.

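### Enrolment runs to 20+6 weeks but miscarriage ends at 20+0: with logistic regression and no term for gestational age at entry, the herbicide–miscarriage association can be biased if exposure is related to entry week

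*Protocol article*

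**What the plan says.** **Entry.** The protocol article, Recruitment, states that adults "who are being seen at prenatal clinics and who are ≤ 20 + 6 weeks gestation will be recruited". Study visits and specimen collection allows recruitment after 13 weeks, with the first specimen then taken as soon as possible after enrolment.

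**Outcome.** Outcomes defines miscarriage as delivery of a liveborn fetus or of "a fetus who experienced fetal death for any cause before 20 + 0 weeks’ gestation". It then divides the outcome: "A miscarriage is considered early if delivery occurs at < 14 + 0 weeks and late if it occurs at ≥ 14 + 0 weeks’ gestation".

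**Role.** Pregnancy loss is one of the Phase 1 hypotheses (Design of the heartland study). Outcomes states: "Primary fetal/newborn outcomes being evaluated are miscarriage, stillbirth", followed by other items. Challenges and anticipated responses adds that "it may be appropriate to evaluate fetal death as an aggregate variable including stillbirth and miscarriage".

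**Model.** Statistical analysis offers logistic regression, by way of example, for dichotomous outcomes. Of the adjusted analyses it says: "We will begin with simple multiple logistic regression models but will adjust to other appropriate models based on the data". It also promises, in general terms, methods suited to the data structure. The a-priori confounder list includes prenatal care, insurance coverage, socioeconomic status and rurality, but not gestational age at enrolment. The article mentions neither delayed entry nor a restricted risk set, and no time-to-event model for loss.

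**The concern.** A loss can be observed only after enrolment, so this is left truncation. Someone entering at 9 weeks is followed through weeks in which loss is comparatively common. Someone entering at 17 weeks is followed for about three weeks in which it is rare. Someone entering at 20+0 to 20+6 cannot be a case, and nobody entering from 14+0 can have an early miscarriage. A logistic model without entry week treats all of them as having had the same opportunity to miscarry.

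If higher exposure goes with later entry, exposed participants have shorter and safer observation, and the odds ratio is pulled down. If higher exposure goes with earlier entry, it is pushed up. Possible links are site, season, rurality and access to care. The sampling schedule could supply another: the first urine is taken at or soon after enrolment, so if urinary concentration changes with gestation (an assumption), a first-sample exposure would follow entry week. A false association with miscarriage could appear, or a real one be hidden. A fetal-death aggregate inherits the problem through its miscarriage component.

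**Working it through.** **1. The windows (protocol article, Recruitment and Outcomes)**

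| Gestation at entry | Early miscarriage observable? | Any miscarriage observable? |
|---|---|---|
| before 14+0 | yes, from entry to 14+0 | yes, from entry to 20+0 |
| 14+0 to 19+6 | no | yes, from entry to 20+0 |
| 20+0 to 20+6 | no | no |

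This step needs no assumption.

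**2. The plan's own effect sizes, as a yardstick.** The article gives no case count, risk or power for miscarriage. The nearest figure is the detectable odds ratio per SD for secondary outcomes, 1.3 to 1.7, at a type I error of 0.0083 = 0.05/6. It reproduces from

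ln OR = (z for 1 − α/2 + z for power) / √[N p(1 − p)(1 − R²)]

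with N = 1,800 (the article's analysable number, taken as stated), p = 288/1,800 = 0.16 and 54/1,800 = 0.03. The 80% power and covariate R² of 0.20 are stated for the primary outcome and assumed to carry over. Result: 1.28 at p = 0.16 and 1.71 at p = 0.03. Bias is judged against effects of this size.

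**3. Remaining risk by entry week.** The hazards are assumed, because the documents give none: 2.5% per week before week 8, 1.5% in weeks 8–9, 0.8% in weeks 10–11, 0.4% in weeks 12–13 and 0.2% in weeks 14–19. The risk of an observed miscarriage for entry at week e is

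R(e) = 1 − product over weeks e to 19 of (1 − weekly hazard).

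For example, R(14) = 1 − 0.998⁶ = 1.2%, and R(12) = 1 − 0.996² × 0.998⁶ = 2.0%.

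| Entry week | 6 | 8 | 10 | 12 | 14 | 16 | 18 | 20+0 on |
|---|---|---|---|---|---|---|---|---|
| Remaining risk | 11.0% | 6.4% | 3.5% | 2.0% | 1.2% | 0.8% | 0.4% | 0 |

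**4. Effect on the odds ratio.** These hazards were used to simulate 1.5 million pregnancies per scenario. Entry was spread evenly over weeks 6 to 20 (assumed), and the exposure–entry correlation was varied. No other covariate was modelled, so the correlation should be read as what remains after the listed confounders.

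| Correlation | Crude logistic OR, truth 1.00 | Crude logistic OR, true HR 1.30 |
|---|---|---|
| −0.3 | 1.34 | 1.76 |
| −0.2 | 1.20 | 1.60 |
| −0.1 | 1.11 | 1.46 |
| 0 | 1.00 | 1.31 |
| +0.1 | 0.90 | 1.20 |
| +0.2 | 0.81 | 1.07 |
| +0.3 | 0.74 | 0.97 |

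A delayed-entry person-week model returned 0.99–1.00 under the null and 1.29–1.31 under HR 1.30 in every row. Logistic regression with entry week added, limited to entry before week 20, returned 0.99–1.00 and 1.31–1.33.

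**5. Sensitivity, at the study's size.** This set used 300 to 600 cohorts of 2,000, entry between 8 and 20+6 weeks but not evenly spread, and a weekly hazard falling from about 1.3% at week 8 to 0.12% at week 19. That gives about 38 losses.

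- With no true effect, the crude OR was 0.94, 0.87 and 0.81 at correlations of 0.1, 0.2 and 0.3. False-positive rates at nominal 5% were 7%, 13% and 25%.
- At −0.2 the OR was 1.16, with 16–17% false positives.
- With a true HR of 1.5 and correlation +0.2, logistic regression gave 1.30 with 38% power. A delayed-entry Cox model gave 1.51 with 70% power, and held about 5% under the null.
- With evenly spread entry and correlation +0.2, the null OR was 0.82, with 19% false positives.

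**The case against.** **The model is open.** The article presents its models as examples. Miscarriage is not among the logistic examples (pre-eclampsia, gestational diabetes, congenital anomaly), and other models are allowed. A reader might infer that the plan commits to a plain logistic analysis of miscarriage; the text does not say so. What remains is that logistic regression is the only model named for a dichotomous outcome, and that leaving the choice to the data commits to no correction. Left truncation is known now from the entry rule, and a fitted logistic model need show no sign of it.

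**Detail of this kind belongs in a fuller document.** Risk sets and outcome-specific models often do, and that document is not shown. The point is therefore limited to a misfit among things the article does state: its entry window, outcome window, starting model and a-priori covariate list.

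**The listed covariates may absorb the link.** Rurality, prenatal care, insurance and socioeconomic status are listed, distance to facilities may be explored, and specimens are to be evaluated by phase of the growing season. This stands in part: only the correlation left after adjustment matters, and its size is unknown. None of these is gestational age at entry, and site is not listed.

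**The size is soft.** Hazards, entry patterns and correlations are all assumed. First collection ideally falls before 13 weeks, so evenly spread entry is probably the less natural case. A 7% false-positive rate, with a Monte Carlo standard error of about 1.0–1.5 points, is hardly distinguishable from 5%. This also stands.

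**The weight is limited.** The study's primary outcome is gestational age at birth, miscarriage has no power statement, and the aggregate is only a possibility. Miscarriage is nevertheless a Phase 1 hypothesis and is listed as a primary fetal/newborn outcome.

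**Conclusion.** The point holds in conditional form. From the article's own definitions, observable miscarriage risk depends on entry week and is zero from 20+0. The one model named for dichotomous outcomes, with the stated covariate list, does not allow for that. Bias follows whenever herbicide level is related to entry week after the listed covariates.

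A reader might go further and infer that the association is biased as planned. The documents do not support this: they report no relation between exposure and entry week, and at zero correlation the crude estimate is essentially right (1.00 for a true 1.00; 1.31 for a true HR of 1.30).

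Under the assumptions above, a residual correlation of ±0.1 to ±0.2 moves a null odds ratio per SD to roughly 0.8–0.9 or 1.1–1.2. The less even entry pattern gives the smaller shifts (0.94 at +0.1, 0.87 at +0.2). Set against detectable odds ratios of 1.3 to 1.7 for other outcomes, that could mask much of an effect near the lower end: at +0.2 a true 1.30 appears as 1.07. The change should be made, because it is nearly free and is needed before anyone can know whether the correlation exists.

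**What to change.** State in the analysis plan that miscarriage, and any fetal-death aggregate, will be analysed with a Cox or discrete-time hazard model on the gestational-age scale:

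- Each participant joins the risk set at gestational age at enrolment.
- Follow-up runs to loss or 20+0 for miscarriage, and to loss or birth for the aggregate.
- Entrants at 20+0 or later are left out of the miscarriage risk set, and entrants at 14+0 or later out of the early-miscarriage risk set.

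If logistic regression is kept, make the same exclusions and add gestational age at enrolment as a covariate. In the simulation this removed the bias about as well.

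The cost is wording only. Gestational age is already assessed for eligibility, and outcomes come from chart review. The small downside is that this outcome would be reported as a hazard ratio rather than an odds ratio.
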